**Methods:**

Three-arm, pragmatic parallel-design randomised controlled trial involving 415 people aged ≥45 and ≤ 80 years, with body mass index ≥28 kg/m^2^ and < 41 kg/m^2^ and painful knee osteoarthritis. Recruitment is Australia-wide amongst Medibank private health insurance members. All three groups receive access to a bespoke website containing information about osteoarthritis and self-management. Participants in the *Exercise* group also receive six consultations with a physiotherapist via videoconferencing over 6 months, including prescription of a strengthening exercise and physical activity program, advice about management, and additional educational resources. The *Exercise plus weight management* group receive six consultations with a dietitian via videoconferencing over 6 months, which include a very low calorie ketogenic diet with meal replacements and resources to support behaviour change, in addition to the interventions of the *Exercise* group. Outcomes are measured at baseline, 6 and 12 months. Primary outcomes are self-reported knee pain and physical function at 6 months. Secondary outcomes include weight, physical activity levels, quality of life, global rating of change, satisfaction with care, knee surgery and/or appointments with an orthopaedic surgeon, and willingness to undergo surgery. Additional measures include adherence, adverse events, self-efficacy, and perceived usefulness of intervention components. Cost-effectiveness of each intervention will also be assessed.

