### Outcomes

Outcome measures and time points are described in Table 4. Our primary and secondary outcome measures are recommended and validated for knee OA trials [56, 57] and are measured at baseline, 6 and 12 months.

**Table 4 Tab4:** Summary of measurements to be taken

Domain	Data collection instrument	Time points		
		Baseline	6 M	12 M

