**Secondary outcome measures**				
Weight	Self-reported	✓	✓	✓
Physical activity	IPEQ-W questionnaire	✓	✓	✓
Health-related quality of life	AQoL-8D questionnaire	✓	✓	✓
Perceived change since baseline	Overall change, 7-point ordinal scale		✓	✓
	Change in pain, 7-point ordinal scale		✓	✓
	Change in function, 7-point ordinal scale		✓	✓
	Change in physical activity, 7-point ordinal scale		✓	✓
Satisfaction with care	7-point ordinal scale		✓	✓
Appointment with orthopaedic surgeon	Yes/No	✓	✓	✓
Depression, anxiety, and stress	DASS-21	✓	✓	✓
Surgery performed	Self-reported TKJR and arthroscopy		✓	✓
Willingness to undergo surgery	5-point ordinal scale	✓	✓	✓

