**Other measures**				
Health economic data	Quality adjusted life years	✓	✓	✓
	Self-reported medication use	✓	✓	✓
	Self-reported use of health services/co-interventions	✓	✓	✓
	Cost-effectiveness ratio		✓	✓
	Work productivity (WHO HPQ Short Form)	✓	✓	✓
Adherence	Number of consultations with physiotherapist^a^		✓	
	Number of consultations with dietitian^b^		✓	
	Duration of consultations with physiotherapist^a^		✓	
	Duration of consultations with dietitian^b^		✓	
	Self-rated adherence to strengthening exercise^a^/ physical activity^a^/weight management^b^, 11-point NRS		✓	
Perceived usefulness	Times accessed website, 5-point ordinal scale		✓	✓
	Usefulness of website, 11-point NRS		✓	
	Usefulness of physiotherapy consultations^a^ 11-point NRS		✓	
	Usefulness of dietitian consultations^b^ 11-point NRS		✓	
	Usefulness of educational resources^a^ 11-point NRS		✓	
	Usefulness of Fitbit^a^ 11-point NRS		✓	
	Usefulness of ketogenic diet^b^ 11-point NRS		✓	
	Usefulness of strengthening exercise program^a^ 11-point NRS		✓	
	Usefulness of physical activity plan^a^ 11-point NRS		✓	
	Video software ease of use^a^ 11-point NRS		✓	
Harms	Adverse events		✓	✓
Determinants	Self-efficacy for symptom control (ASES)	✓	✓	✓
	Self-efficacy for eating (WELQ)	✓	✓	✓
	Attitudes towards self-management (PAM-13)	✓	✓	✓
	Treatment beliefs about arthroplasty (TOA)	✓	✓	✓
	Fear of movement (BFMS)	✓	✓	✓
Long-term surgical rates	Number who have had arthroscopy/arthroplasty		24 months and 60 months	

*NRS* Numeric rating scale, *WOMAC* Western Ontario and McMaster Universities Osteoarthritis Index, *IPEQ-W* Incidental and Planned Exercise Questionnaire, *AQoL-8D* Assessment of Quality of Life Instrument, *DASS* Depression, Anxiety, and Stress Scale, *TKJR* Total knee joint replacement, *WHO HPQ* World Health Organization Health and Work Performance Questionnaire, *ASES* Arthritis Self-efficacy Scale, *WELQ* Weight Efficacy Lifestyle Questionnaire, *PAM* Patient Activation Measure, *TOA* Treatment beliefs in knee and hip OA – arthroplasty subscale, *BFMS* Brief Fear of Movement Scale for osteoarthritis

^a^measured in *Exercise* and *Exercise plus weight management* groups only

^b^measured in *Exercise plus weight management* group only

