Economic evaluations will assess and compare the cost-effectiveness of the interventions. This will involve analysis of: i) cost per extra person with a clinically significant improvement in pain (measured as 1.8 point reduction on the pain score) and function (6 unadjusted WOMAC units), and; ii) per quality-adjusted life years (QALYs) gained for the intervention compared to control at 12 months. QALYs will be calculated based on utility scores using the AQoL-8D at baseline and 12 months. The difference in health care usage and productivity lost between baseline and 12 months will be compared for intervention and control groups. The association between utility gains on the AQoL-8D and productivity will also be compared between the intervention and control groups.

To evaluate the longer-term effects of the *Exercise* and *Exercise plus weight management* interventions on total knee joint replacement and knee arthroscopy surgical rates, logistic regression models for surgery will be fit using generalised estimating equations to account for clustering by physiotherapist and dietitian, with treatment effects summarised using risk differences and 95% confidence intervals. The stratifying variable of history of knee surgery will be adjusted for.

To evaluate whether there is a relationship between amount of weight loss and changes in pain and/or function, linear regression models for changes in pain and outcome will be fit and will include a term for weight lost at 6 and 12 months (as percentage of baseline weight), adjusting for baseline level of the outcome, assigned treatment group, and stratifying variables. Demographic variables thought to affect both weight loss and outcomes levels, including age and sex, will also be included in the model. Fractional polynomial terms for weight lost will be assessed to investigate if the relationship between outcomes and weight loss is non-linear. Standard diagnostic plots will be used to assess regression assumptions. We will also evaluate whether there is a relationship between adherence to exercise and changes in pain and/or function by estimating a complier-average causal effect using a two-stage least squares approach [76].

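### The economic analysis bases 12-month QALYs on baseline and 12-month utilities only, in conflict with Table 4; omitting the 6-month utility biases incremental QALYs and cost per QALY in general, in a direction the documents do not fix

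*Protocol article*

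**What the plan says.** The economic paragraph of the Analysis section sets two endpoints. One is cost per additional person with a clinically significant improvement; the other is cost per "quality-adjusted life years (QALYs) gained for the intervention compared to control at 12 months". For the second it gives this rule: "QALYs will be calculated based on utility scores using the AQoL-8D at baseline and 12 months". It names no formula and gives no reason for using two visits.

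The data collection plan is wider:

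- The Outcomes section says that the primary and secondary measures "are measured at baseline, 6 and 12 months".
- In Table 4, the row "AQoL-8D questionnaire", under secondary outcomes, is ticked at all three visits.
- In the health economic rows of Table 4, "Quality adjusted life years" is also ticked at all three, and "Cost-effectiveness ratio" at 6 and 12 months.

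Treatment fills the first half of the year: the abstract describes "six consultations with a physiotherapist via videoconferencing over 6 months", with dietitian contact over the same period in the combined arm. The abstract also says "Primary outcomes are self-reported knee pain and physical function at 6 months".

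**The concern.** A QALY total is utility accumulated over time, so a 12-month total depends on the path between the visits as well as on its ends. Followed as written, the sentence discards the one intermediate utility that the trial measures, at the end of treatment and at the primary time point. The gain over the first six months would then be inferred from the 12-month value alone.

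The abstract makes cost-effectiveness part of the aim, and the Design section places it among the main trial results. The Background says it is unknown whether diet plus exercise is more cost-effective than exercise alone. If the arms follow different paths after treatment ends, the error differs between arms and could affect how they compare. A rule that conflicts with the schedule also leaves room to choose the method after the results are known.

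**Working it through.** **The plan's own figures.** The article states no QALY or cost-per-QALY figure, so there is none to reproduce. Its sample size does reproduce and does not depend on this point. With correlation 0.4, 80% power, two-sided 0.05 and 15% loss:

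- effect size 0.3 at 1:1 needs 147 per arm, and 147/0.85 rounds up to 173;
- effect size 0.4 at 2.5:1 needs 58 controls, and 58/0.85 rounds up to 69;
- 2 × 173 + 69 = 415, as stated.

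**Inputs.** The visits (0, 6 and 12 months) and the 12-month horizon come from the article. The utility differences d6 and d12 are not given and are assumed below. The baseline difference is taken as zero.

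**Formulas**, in years, joining the points by straight lines:

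- Three visits: 0.5 × (0 + d6)/2 + 0.5 × (d6 + d12)/2 = 0.5·d6 + 0.25·d12
- Two visits: 1 × (0 + d12)/2 = 0.5·d12
- Three-visit minus two-visit: d6/2 − d12/4, which is zero only if d6 = d12/2

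**Scenarios (all utilities assumed).** The last column is the two-visit cost per QALY divided by the three-visit value. For a given incremental cost, this equals the inverse ratio of the QALY gains.

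| Course of benefit | d6 | d12 | Two-visit QALYs | Three-visit QALYs | Error in QALYs | Cost per QALY ratio |
|---|---|---|---|---|---|---|
| Fully maintained | 0.06 | 0.06 | 0.030 | 0.045 | 33% too low | 1.5 |
| Half retained | 0.06 | 0.03 | 0.015 | 0.0375 | 60% too low | 2.5 |
| None retained | 0.06 | 0 | 0 | 0.030 | 100% too low | undefined |
| Linear growth to 12 months | 0.03 | 0.06 | 0.030 | 0.030 | none | 1.0 |
| Builds mainly after 6 months | 0.02 | 0.06 | 0.030 | 0.025 | 20% too high | 0.83 |

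The percentages depend only on d12/d6, not on the absolute size of the utilities.

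**A different two-visit method.** Since no formula is named, suppose instead that the 12-month difference is credited for the whole year, giving 1 × d12. Against 0.5·d6 + 0.25·d12:

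- with d12 = d6 it gives 1.00·d6 against 0.75·d6, one third too high;
- with d12 = d6/2 it gives 0.50·d6 against 0.625·d6, 20% too low;
- it agrees when 0.75·d12 = 0.5·d6, that is, d12 = two thirds of d6.

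The size and even the sign of the error therefore depend on the method as well as on the course of benefit.

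**Consistency with Table 4.** A cost-effectiveness ratio is scheduled at 6 months. If that ratio is per QALY, it cannot be computed from baseline and 12-month utilities. If it is per responder, it can; the table does not say which.

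**The case against.** The strongest reply is that the sentence is loose wording for the 12-month horizon. The sentence that follows it compares health care use and lost productivity over the interval from baseline to 12 months, and Table 4 already schedules QALYs at every visit. A fuller economic plan may exist. That reading is possible, but the sentence names two visits rather than an interval. If all three were intended, the wording still needs correcting to agree with the table.

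The reply also rightly limits what can be claimed. A reader might infer that the rule necessarily works against the active arms, because the effect should peak at 6 months. The documents do not say so. Some features make waning plausible: treatment ends at 6 months, the diet was chosen partly for short-term weight loss, and there is advice for regain. Others point towards maintenance: the design aims at long-term self-management, there is a weight maintenance phase, and website access runs to the 12-month questionnaire. No utility path is stated.

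A reader might also infer that cost accumulation is defective in the same way. That is not supported: the article's comparison of use and productivity can cover the whole year, and nothing shows that the 6-month questionnaire is left out of it.

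**Conclusion.** The point holds as an internal conflict and as a poorly fixed rule. The Analysis section leaves out a utility that Table 4 schedules for exactly this purpose, and doing so biases incremental QALYs and cost per QALY in general.

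Under straight-line interpolation and no baseline difference, the discrepancy is d6/2 − d12/4. The 33%, 60% and 100% understatements illustrate full, half and no retention of the 6-month benefit; they are not estimates for this trial. The discrepancy vanishes for linear growth over the year and reverses if benefit comes mainly later. What stands without any assumption about the course of benefit is that a measured point on the curve should not be replaced by interpolation.

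The consequence is confined to the cost-per-QALY analysis. The primary outcomes, their analysis and the sample size of 415 are unaffected.

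**What to change.** Replace the QALY sentence in the Analysis section with:

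> QALYs over 12 months will be calculated as the area under the curve (trapezoidal rule) from AQoL-8D utilities at baseline, 6 and 12 months, with between-group differences adjusted for baseline utility.

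This names the formula, brings the text into line with Table 4, and allows for chance baseline imbalance, which the algebra above sets to zero.

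The cost is one sentence, settled before the data are analysed. It needs no new visit, questionnaire or participant burden, because the AQoL-8D is already scheduled at 6 months. No change to how costs are accumulated is shown to be needed.

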Fulfil National Institute for Health and Care Excellence [3] clinical criteria for osteoarthritis: • Age > 45 years; • Have activity related joint pain; and • Have morning stiffness ≤30 min. Average knee pain severity ≥4 on 11-point numeric rating scale (NRS, where 0 = no pain, 10 = worst pain possible) in the past week History of knee pain on most days for at least 3 months Aged < 81 years – due to potential safety reasons and additional co-morbidities Body mass index (BMI) ≥ 28 kg/m^2^ and < 41 kg/m^2^. The lower BMI limit was chosen according to recommendations [39] that VLCD are effective in supporting weight loss in people with a BMI > 27. The upper limit was chosen as these individuals often require more extensive intervention and for possible safety reasons Member of Medibank with a level of cover that includes arthroplasty surgery Able to give informed consent and to participate fully in the interventions and assessment procedures Willing to follow advice for self-management, participate in exercise/physical activity and/or participate in a weight loss program if part of their treatment program Have the ability to weigh themselves (e.g. have access to the same set of bathroom scales)	Booked for knee surgery on either knee Have had all eligible knee joints replaced by arthroplasty Knee surgery within the past 6 months Unable to speak or read English Self-reported diagnosis of rheumatoid arthritis or other inflammatory arthritis Other medical condition or upcoming medical procedures that in the opinion of the research staff and/or investigators would preclude participation Private health insurance claims related to cancer treatment or inpatient neurological rehabilitation in the previous 12 months, palliative care, or acquired brain injury Unable to use/access a telephone and internet For those identified as at risk from the pre-exercise and falls screening, doctor does not give clearance Used low-calorie meal replacement products (e.g. Optifast/Optislim) for weight loss in previous 6 months Currently, or in the past 6 months, undertaking regular strengthening exercises for the knee Unable to undertake VLCD for medical reasons including: i. Self-reported diagnosis of Type 1 diabetes ii. Self-reported Type 2 diabetes requiring insulin or other medication apart from metformin iii. Self-reported warfarin use iv. Stroke or cardiac event in previous 6 months v. Unstable heart condition vi. Fluid intake restriction

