### Additional measures

*Economic data*: assessed by self-reported medication use and healthcare costs (regarding the use of health services), quality-adjusted life years (QALY), cost-effectiveness ratio (calculated using predictions of health care costs and QALYs), and work productivity (using the World Health Organisation Health and Work Performance Questionnaire [70]). Knee surgery costs will be obtained by linking to Medibank data.

*Adverse events*: any undesirable clinical occurrence, whether considered to be treatment-related or not, that includes a clinical sign, symptom, or condition, are self-reported in questionnaires and recorded by the clinician during the consultation. Participants are asked to provide details on the nature of the event, how long it lasted for, and what action they took.

*Adherence*: assessed by recording the number of consultations received from the physiotherapist and/or dietitian. Adherence to prescribed exercise and physical activity programs is self-reported by the participant via questionnaire, being scored on an 11-point NRS (0 = not at all and 10 = completely as instructed). Adherence to the weight management plan, if applicable, is also self-reported and scored on a similar 11-point NRS.

*Perceived usefulness of treatment components*: assessed by self-report with response options ranging from 0 = “not at all” to 10 = “extremely useful”. Usefulness questions relate to the information on the website, consultations with the physiotherapist and/or dietitian, resource booklets, Fitbit, VLCD, strengthening exercise program, and physical activity plan. Participants will also be asked how many times they accessed the website in the last 6-months (5-point scale ranging from “never” to “> 10 times”) and how easy it was for them to use the videoconferencing software (11-point NRS ranging from 0 = “not at all easy” to 10 = “extremely easy”).

*Long-term surgical rates*: via linkage with the data routinely collected by Medibank Private, and will include the number of individuals who had a knee arthroscopy and/or arthroplasty intervention at 2 and 5 years after baseline. These findings will be reported separately from the main trial outcomes.

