### Analysis

We will use intention-to-treat analyses, using multiple imputation to account for missing data and details on the imputation will be reported [74]. Participants will be included in their randomised treatment groups regardless of their post-randomisation behaviour. *P* values less than 0.05 will be considered significant. Outcomes (primary, secondary, and determinants) will be compared between groups as follows: i) *Exercise* vs *Exercise plus weight management*; ii) *Exercise* vs control, and; iii) *Exercise plus weight management* vs control. For continuous data, mean differences in change over time between these groups will be estimated using linear regression models fit to data from both follow-up time points, with random effects for participants, and accounting for clustering by physiotherapist and dietitian in the *Exercise* and *Exercise plus weight management* groups. Models will be adjusted for the stratification variable (history of knee surgery) and values of the outcome at baseline. Terms for time and treatment will be included, with an interaction between the two. Regression assumptions will be assessed using standard diagnostic plots. For binary outcomes, logistic regression models will be fit using generalised estimating equations to account for clustering, with risk differences and 95% confidence intervals calculated. This will include a comparison of the proportion of participants in each group whose improvement meets or exceeds the minimal clinically important difference for each of the primary outcomes. For ordinal outcomes, proportional odds models will be fit similarly. Multinominal models will be applied if the assumption of proportional odds is not valid. To assess the sensitivity of the results for the primary outcomes in situations in which the outcomes are missing not at random, we will apply a pattern-mixture approach that involves fitting regression models that adjust for departures from the missing at random assumption [75].

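### Long-term knee surgery is read from one insurer's records as a yes/no outcome, with no provision for members whose arthroplasty cover ends before 2 or 5 years

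*Protocol article*

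**What the plan says.** All references are to the protocol article.

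- **Source and outcome.** Under Additional measures, long-term surgical rates are obtained "via linkage with the data routinely collected by Medibank Private" and consist of the "number of individuals who had a knee arthroscopy and/or arthroplasty intervention at 2 and 5 years after baseline". Table 4 gives the times as 24 and 60 months. The findings are to be reported apart from the main results.
- **Model.** Under Analysis, "logistic regression models for surgery will be fit using generalised estimating equations to account for clustering by physiotherapist and dietitian". Arms are compared by risk difference with a 95% interval, and history of knee surgery is an adjustment variable.
- **Cover.** Table 1 has the inclusion criterion "Member of Medibank with a level of cover that includes arthroplasty surgery". No section asks for cover to continue, or to be recorded, after entry.
- **Other surgery data.** Table 4 has self-reported surgery at 6 and 12 months only.
- **Missing data.** The general rule under Analysis is: "We will use intention-to-treat analyses, using multiple imputation to account for missing data and details on the imputation will be reported". The pattern-mixture sensitivity analysis is confined to the primary outcomes.

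**The concern.** The insurer's data can show an operation only while the person holds relevant cover. After that, surgery elsewhere leaves no record, and in a count of individuals with surgery the missing record looks the same as a true negative. Length of observation therefore differs between people, while a fixed-time yes/no model treats it as equal. Self-report stops at 12 months, so no second source corrects years 2 to 5.

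At stake are the absolute surgery risks and the risk differences between arms. If lapse is equal across arms, the difference is diluted. If lapse depends on arm, the difference is biased even when surgery rates are the same. Unequal lapse is plausible: two arms receive a clinician-delivered service in a trial funded by the insurer, while the control arm receives a website.

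**Working it through.** **The plan's own figures.** The document gives no surgery, lapse or death rate and no power for this outcome. Its sample size (173, 173 and 69, total 415) rests on the 6-month outcomes. It reproduces (147/0.85 and 58/0.85, rounded up) but does not bear on this question beyond giving the arm sizes. Every rate below is an assumption.

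**Step 1. Equal lapse, 5 years, no deaths.** Assume true 5-year surgery risks r of 25% and 17.5%, and constant hazards: surgery h = −ln(1 − r)/5, lapse λ = −ln(1 − annual lapse).

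- Recorded risk, lapsed counted as no surgery: h/(h + λ) × [1 − exp(−5(h + λ))].
- Probability of lapsing first: λ/(h + λ) × [1 − exp(−5(h + λ))].
- Risk with lapsed members dropped: recorded risk ÷ (1 − probability of lapsing first).

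At 3% lapse, λ = 0.03046.

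- For r = 25%, h = 0.05754. The recorded risk is (0.05754/0.08800) × (1 − 0.6441) = 23.3%.
- For r = 17.5%, h = 0.03847. The recorded risk is (0.03847/0.06893) × (1 − 0.7085) = 16.3%.
- The difference is 7.0 points. Dropping lapsed members gives 0.2327/0.8768 = 26.5% and 0.1627/0.8712 = 18.7%.

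Differences in the table come from unrounded risks.

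| Lapse per year | Counted as no surgery | Difference (true 7.5) | Shortfall | Lapsed dropped | Difference |
|---|---|---|---|---|---|
| 3% | 23.3% vs 16.3% | 7.0 | 7% | 26.5% vs 18.7% | 7.9 |
| 5% | 22.2% vs 15.5% | 6.7 | 11% | 27.7% vs 19.5% | 8.1 |
| 10% | 19.7% vs 13.7% | 6.0 | 21% | 30.8% vs 22.0% | 8.8 |

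With true risks of 15% and 10.5% (difference 4.5), counting lapsed as no surgery gives 4.2, 4.0 and 3.5, so the same 7%, 11% and 21% shortfalls.

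**Step 2. Unequal lapse, no true effect.** Take a 20% 5-year risk in both arms (h = 0.04463), with lapse of 5% a year in one and 10% in the other. Counting lapsed as no surgery gives 17.7% and 15.7%, a spurious 2.0 points. Dropping them gives 22.3% and 24.9%, about 2.7 points in the other direction.

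**Step 3. Death alone.** Take 5-year risks of 20% and 12% before deaths, a death hazard of 0.01 a year and no lapse. The cumulative incidence with death competing is 19.5% and 11.7%, a difference of 7.8. Keeping the dead as no surgery gives exactly these figures. Dropping the dead gives 20.4% and 12.3%, a difference of 8.1.

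**Step 4. Two years.** Take 2-year risks of 10% and 6%, a death hazard of 0.01, and lapse hazards of 0.02, 0.05 and 0.10 a year. The true difference is 4.0. Counting lapsed as no surgery gives 3.9, 3.8 and 3.6. Dropping them gives 4.0, 4.1 and 4.3.

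**Step 5. Against sampling error.** At 17.5% and 25%, the standard error of the risk difference for 173 vs 69 is √(0.175 × 0.825/173 + 0.25 × 0.75/69) = 6.0 points, so a 95% interval of about ±11.7. For 173 vs 173 it is 4.4 points, about ±8.6. The 0.5 to 1.5 point dilution in step 1 is therefore about 0.1 to 0.35 standard errors.

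**The case against.** The strongest reply is that the Analysis section already plans multiple imputation. A lapsed member's later status is missing data, and how it is defined belongs in an analysis plan that is not shown. This stands in part. A reader might infer that a logistic model cannot handle lapse, and the document does not support that. But imputation works only if end of cover is known and later status is set to missing, and neither the linkage description nor the analysis text provides for this. Without cover dates nothing looks missing, so nothing is imputed. The data source and the model are fixed in the published text.

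Three further stronger readings also fail:

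- **Death as a second flaw.** Step 3 shows that the dead, kept as no surgery, give the correct cumulative incidence. The document does not say that they will be dropped.
- **Bias always toward zero.** That follows from counting lapsed members as no surgery. Dropping them errs the other way.
- **Equal damage at both times.** At 2 years the shift in step 4 is at most about 0.4 on a 4-point difference.

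It is also fair to say that the sizes are assumed and are small beside sampling error (step 5), that risk at a fixed time is a legitimate target, and that this outcome is reported separately. These points limit the severity. They do not remove a systematic error that can be avoided cheaply.

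**Conclusion.** The concern holds in limited form. As written, the analysis makes no provision for cover that ends before 2 or 5 years, and a lapsed member who later has surgery is recorded as having had none. Under constant hazards and assumed lapse of 3% to 10% a year, equal in both arms, a 7.5-point 5-year difference appears as about 7.0 to 6.0. Under the assumed 5% against 10% lapse, a difference of about 2 points appears where none exists. The actual size depends on surgery and lapse rates that the document does not give. The issue matters mainly at 5 years, does not concern deaths kept as no surgery, and leaves the 6-month primary conclusions untouched. The change is worth making before the linkage data are requested.

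**What to change.** - **Data.** Ask in the same linkage for cover end dates, procedure dates and, where available, death dates. The document does not say which dates the insurer's data hold, so the request should name them.
- **Analysis.** Estimate cumulative incidence of arthroplasty, and separately of arthroscopy, from randomisation. Censor at end of eligible cover and treat death as a competing event.
- **Reporting.** Keep the planned summary: risk differences at 2 and 5 years with 95% confidence intervals, adjusted for history of knee surgery. Pseudo-value or censoring-weighted generalised estimating equations would do this and retain the planned allowance for clustering by physiotherapist and dietitian. A Cox model stratified only by surgery history would lose that allowance.
- **Transparency.** Report lapse by arm.

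The cost is a few extra linkage fields and revised wording for a separately reported analysis. The downside is the assumption that lapse is non-informative given arm and stratum, and reporting lapse by arm lets readers judge it.
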